#### *Anthropometric and body composition measures*

Anthropometric measures include body mass obtained to the nearest 0.1 Kg without shoes using an electric scale, and stature (measured without shoes, jackets, or other heavy clothing) at the end of inhalation to the nearest 0.1 cm using a wall-mounted stadiometer. BMI will be computed by dividing body mass (kg) by stature (m^2^) and BMI percentile values will be determined from the Centers for Disease Control growth charts [58]. Percentage of body fat and lean mass will be measured in a supine position using dual x-ray absorptiometry (DXA) scan (Lunar Prodigy Advance Plus; GE Healthcare, Milwaukee, WI). This specific DXA unit provides a reliable and accurate measurement of distribution of lean and fat mass [59]. We will perform regional fat mass and lean mass calculations, in addition to total body analysis, using the enCORE pediatric software version 12.30.008, which automatically demarcates the regional boundaries for all regions.

#### *Health-related quality of life*

The measurement of health-related quality of life provides information about physical, emotional, social, and school components of wellbeing based on the calculation of two summary scores (i.e., physical and psychological). For this measurement we will use the validated 23-item PedsQL™ 4.0 Generic Scale [60]. This measure has shown good reliability and validity in children and adolescents ages 2-18 years old [60]. In addition, parents will complete the parent version of the PedsQL scale. Both measurements will be used to evaluate changes in quality of life. For participants with PWS we will first determine the test-retest reliability of this instrument at two time intervals separated by one week to decide if this measurement is reliable and is acceptable for use.

#### *Child’s self-efficacy for physical activity*

Self-efficacy for physical activity will be measured with an eight item questionnaire rated on a five point scale ranging from disagree a lot to agree a lot [61-64]. This questionnaire was originally developed for use with children in fifth grade, but also validated with children in eighth grade [61-64]. This questionnaire had a test-retest reliability of r=0.84 over a period of two weeks. Additionally, the questionnaire had an internal consistency score of 0.88 [62,63]. For participants with PWS we will first determine the test-retest reliability of this instrument at two time intervals separated by one week to decide if this measurement is reliable and is acceptable for use.

#### *Dietary intake*

To help interpret whether changes in body composition can be solely attributed to the PA intervention, dietary intake will also be assessed at the same time points as the other variables of interest. The participating parent or legal guardian will maintain a food record of the child’s diet during two days of the week and one day on the weekend. In this record the parent will include quantity of food and fluids consumed, the preparation method, and the brand of the product. Before the baseline measurement, parents will attend a training session with a registered dietitian to learn how to estimate portion sizes and keep a food record. The information collected through the food records will be entered into The Food Processor, ESHA Research, Salem, OR, USA program and analyzed for macronutrient percent intake and total calories.

#### Parent measurements

The parent who consents to participate in the study will provide demographic (ethnicity, family income, occupation, primary language spoken at home, etc.) and medical information (e.g., child’s medical history, current conditions related to the child’s ability to engage in physical activity, medications use, intelligence scores in the case of children with PWS). Each parent will also complete several questionnaires to measure the following:

##### *Regulatory efficacy for the parent*

Parents’ confidence to regulate and manage their child’s PA will be assessed using a modified version of a proxy efficacy scale for regulating exercise behavior [65]. The original scale will be adapted to reflect the parents’ confidence to regulate and motivate their children to participate in PA. In a survey of parents of children aged 2-18 years, this modification of the proxy efficacy scale has shown excellent reliability (Cronbach Alpha=.98) and an acceptable one week test-retest reliability correlation of .64 [66].

##### *Parental influence*

This scale assesses the regulation (i.e., social control) used by parents to encourage PA behavior in their children [67]. This scale is separated into three types of social control. The two positive types of social control include positive (encouraging) and collaborative (being active with the child). The negative type of social control examines nagging and ordering to be active. In a recent study of parents of children ages 2 to 16 years the reliability of this measure has been shown to be acceptable-to-good for all types of social control: collaborative (Cronbach alpha=.77), positive (Cronbach alpha=.67) and negative (Cronbach alpha=.85) [68].

#### *Process measures*

Qualitative information will also be collected to further evaluate the feasibility of this type of PA intervention. Parents will be asked to provide information in the form of completed checklists addressing the implementation of the specific playground games in terms of difficulty and enjoyment by the children as well as total time spent per session doing the prescribed activities. This information will serve as a form of adherence monitoring as well as a means by which the families can provide feedback to the research team about the content of the intervention.

Additional information will be obtained during on-site feedback sessions conducted at 12- and 24-weeks of the intervention. Parents will be asked about barriers and facilitators for the implementation of the intervention, likelihood of participating in a future project, satisfaction with the study, the influence of participation in the study on their lifestyle, and their child’s overall participation in PA. Parents will also be asked to provide suggestions as to how the intervention could be modified to better serve their individual needs.

### Data analyses

The main purpose of this study is to investigate short-term changes (immediately following the 24-week intervention) in PA, motor proficiency, and health-related outcomes in children with and without disability following completion of a physical activity program conducted in the home environment. A 2 (time: pre, post) by 2 (group: control, intervention) by 2 (youth: obese or PWS) mixed model ANOVA will be used to assess changes in the primary outcome (i.e., physical activity). Similar analyses will also be performed to assess changes in gross motor proficiency, body composition, and central sensory reception and integration. Other changes that will also be evaluated using mixed model ANOVAs include changes in quality of life, child self-efficacy, parent regulatory efficacy, and parent social influences. Potential confounders will serve as covariates where appropriate.

A power analysis was performed using G*Power 3.1.9 to identify the appropriate sample size for a power of .95, an alpha level of .05 and a correlation between time points was assumed to be .50. A small to moderate effect size (*f*=.20) was chosen, given the variability in physical activity expected in children with PWS [15]. A sample size of 84 was identified to provide sufficient power to detect an interaction. Given a 30% probability of drop-outs, 115 children will be recruited.

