**Methods/Design:**

The study participants will be 115 youth ages 8-15 y (45 with the syndrome and 70 without the syndrome but categorized as obese). The study will use a parallel design with the control group receiving the intervention after serving as control. Participants will be expected to complete a physical activity curriculum 4 days a week for 6 months including playground games 2 days a week and interactive console games 2 days a week. Parents will be trained at baseline and then provided with a curriculum and equipment to guide their implementation of the program. Tips related to scheduling and coping with barriers to daily program implementation will be provided. Throughout, parents will be contacted by phone once a week (weeks 1-4) and then every other week to receive support in between visits. Measurements of children and parents will be obtained at baseline, 12 weeks, and at the end (week 24) of the intervention. Children main outcomes include physical activity (accelerometry), body composition (dual x-ray absorptiometry), motor proficiency (Bruininks-Oseretsky Test of Motor Proficiency), quality of life and physical activity self-efficacy (questionnaires). Intervention compliance will be monitored using mail-in daily self-report checklists.

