### The development of the active play @ home curriculum

Considering the abilities, needs, constraints, and preferences of children with PWS and their parents as well as previous intervention approaches that proved successful in this population [18,19] we developed a home-based PA curriculum called Active Play @ Home. This well-rounded and varied PA curriculum includes all the essential exercise components recommended in the national guidelines (progressive games and exercises targeting cardiovascular fitness, muscular strength and endurance) while also targeting motor skill competencies. In addition, the curriculum incorporates the use of interactive console-based games that were carefully chosen to stimulate fitness components as well as specific motor skill competencies. The curriculum therefore blends more traditional playground games and exercises with interactive console-based games. The inclusion of the interactive console-based games aims to provide the children with a choice of activities that can be performed indoors while the playground games can be played outdoors. The curriculum is designed to involve an adult leader and one child; however, all activities can be played with more than one child in the home environment.

The goal of the Active Play @ Home study is to determine if a parent-led PA curriculum incorporating playground games and interactive console-based games can increase levels of PA and lead to positive motor and health-related outcomes in children with PWS and in children without the syndrome but who are obese. Changes in PA and motor and health-related parameters will be evaluated in these two groups in comparison to control groups following a 24-week PA intervention. The primary hypothesis is that an age-appropriate home-based PA intervention will increase PA levels in children with and without PWS. The secondary hypotheses include the following: 1) motor proficiency, central sensory reception and integration, and body composition will significantly improve in children, with and without PWS, following completion of the home-based PA intervention, and 2) self-efficacy and quality of life will increase significantly in children, with and without PWS, who complete the home-based PA intervention.

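### The primary pre/post ANOVA leaves the week-12 measurements unused and gives no weight to a child without week-24 data, with 30% drop-out expected

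*Protocol article*

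**What the plan says.** The Abstract (Methods/Design) gives three measurement times: "Measurements of children and parents will be obtained at baseline, 12 weeks, and at the end (week 24) of the intervention".

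The Data analyses section names the model for the primary outcome, physical activity: "A 2 (time: pre, post) by 2 (group: control, intervention) by 2 (youth: obese or PWS) mixed model ANOVA". It applies similar analyses to motor proficiency, body composition and sensory integration, and mixed model ANOVAs to quality of life and the efficacy and social-influence scales. No stated analysis uses the week-12 outcomes.

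The same section finds that 84 children are needed and raises this to 115 for a 30% probability of drop-out.

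The wording on completion varies:
- Primary hypothesis (curriculum development section): "an age-appropriate home-based PA intervention will increase PA levels in children with and without PWS". Completion is not mentioned.
- Secondary hypothesis 1: change "following completion of the home-based PA intervention".
- Secondary hypothesis 2: "self-efficacy and quality of life will increase significantly in children, with and without PWS, who complete the home-based PA intervention".
- Main purpose (Data analyses): change "in children with and without disability following completion of a physical activity program conducted in the home environment".

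**The concern.** In a mixed-design ANOVA with two time levels, the group x time interaction is a comparison of mean change scores between groups. A child with no week-24 value has no change score and drops out of that test, even if a week-12 value was obtained. Raising 84 to 115 is consistent with this: drop-outs are treated as lost to the analysis.

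Retention could differ between the groups. Intervention families run four sessions a week for 24 weeks, with activity rising from 25 to 45 minutes, and fill in checklists. Wait-listed families receive the programme later, which gives them a reason to stay. The article's own group interviews report that parents may find the time burdensome and that children may become frustrated. If intervention families whose child responds poorly by week 12 leave more often, those who remain look better than the group that started. The effect on physical activity would then be overstated. The week-12 values, which would carry part of the missing information, are not in the model.

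**Working it through.** **Inputs from the Data analyses section.** "A small to moderate effect size (*f*=.20) was chosen", "for a power of .95, an alpha level of .05 and a correlation between time points was assumed to be .50"; required N 84; drop-out 30%; recruited N 115. From Study design: intervention 35 + 50 = 85, wait-list 10 + 20 = 30.

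**Step 1: reproduce 84.** For a repeated-measures within-between interaction with k = 2 groups and m = 2 time points:
- lambda = f² x N x m / (1 - rho) = 0.04 x 84 x 2 / 0.50 = 13.44
- df1 = (k - 1)(m - 1) = 1; df2 = (N - k)(m - 1) = 82
- power from the noncentral F = 0.952, and 84 is the smallest N that reaches 0.95.

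So the study was sized for two groups measured at two times.

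**Step 2: planning difference in SD units.** With rho = 0.50 the variance of a change score is 2(1 - 0.50) = 1 SD². With 42 per group, lambda = d² x 42 x 42 / 84 = 21d². Setting 21d² = 13.44 gives d = 0.80 SD.

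**Step 3: children who leave the test.** 0.30 x 115 = 34.5, so about 34 children.

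**Step 4: conditional illustration of bias.** The article gives one overall drop-out figure and no mechanism, so everything about the mechanism here is assumed. Settings: no true effect, three time points with correlation 0.50 between each pair, 85 versus 30 children, 30% drop-out in each group and all of it after week 12, 1,500 simulated trials per row. In the middle rows, intervention drop-out depends on poor week-12 change (log-odds slope per SD) and control drop-out is random. The two columns that keep all baselines use regression-based estimates of the missing week-24 values.

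| Drop-out mechanism | Completer bias (SD) | All baselines, no week 12 | All baselines plus week 12 | Type I error, completers |
|---|---|---|---|---|
| Unrelated to outcome | 0.00 | 0.00 | 0.00 | 5.1% |
| Intervention only, slope 0.5 | 0.06 | 0.02 | -0.01 | 6.0% |
| Intervention only, slope 1 | 0.12 | 0.05 | -0.01 | 7.2% |
| Intervention only, slope 2 | 0.18 | 0.10 | 0.00 | 11.5% |
| Same in both groups, slopes 0.5 to 2 | -0.01 to 0.00 | -0.01 to 0.00 | -0.01 to 0.00 | 5.1% to 6.2% |

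Simulation error: with about 59.5 and 21 completers, the SE of one trial's difference is √(1/59.5 + 1/21) = 0.25, so the SE of a mean bias is 0.25/√1500 = 0.007. For a 5% error rate it is √(0.05 x 0.95/1500) = 0.6 percentage points. The -0.01 entries are therefore compatible with zero, and 6.0% is barely distinguishable from 5%.

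Against the planning difference: 0.06/0.80 = 8%, 0.12/0.80 = 15%, 0.18/0.80 = 23%.

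**Step 5: a less severe assumption.** If half of the 30% intervention loss is random and occurs before week 12, completer bias falls to about 0.04, 0.08 and 0.10 SD for slopes 0.5, 1.0 and 1.5.

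**The case against.** The strongest reply is that change from baseline to the end of the programme is a legitimate primary contrast, and that leaving week 12 out of the primary model does not show it is unused elsewhere. A condensed article also commonly leaves the analysis set and missing-data handling to the full plan. The choice of contrast stands: the proposed model keeps the same one. The rest stands only in part. The article states the primary model with two time levels, and an analysis plan would have to depart from that model to bring in week 12.

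The term mixed model ANOVA could mean a likelihood fit. That would keep children with a baseline only, but it would still omit week 12 and leaves 0.02 to 0.10 SD of bias in the illustration.

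A reader might infer that the whole plan is a completer analysis. The documents do not support that. The primary hypothesis has no such wording. Only secondary hypothesis 2 restricts itself to completers. The phrasing of secondary hypothesis 1 and of the main purpose can be read as the time of assessment. No text excludes non-completers or ends measurement when a family stops the programme, and stopping the programme is not the same as missing the week-24 visit.

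A reader might also infer that retention will differ by group and that benefit is therefore inflated. That is not established either: the article gives a single drop-out figure, and the bias vanishes when the same mechanism acts in both groups.

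**Conclusion.** The point holds as a weakness in the stated primary model. As written, a child without week-24 data contributes nothing to the group x time test, about 34 of 115 children are expected to be lost, and the week-12 outcomes have no role. The completion wording adds to this clearly in secondary hypothesis 2, less clearly in secondary hypothesis 1 and the main purpose, and not in the primary hypothesis.

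The bias of 0.06 to 0.18 SD (8% to 23% of the 0.80 SD planning difference) is an illustration. It rests on all intervention drop-out occurring after week 12 and depending on week-12 change, with random drop-out among controls. It is smaller if part of the loss is early and random, and about zero if drop-out is unrelated to outcome or acts equally in both groups.

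Severity: should-fix. The better method is concrete and uses data already scheduled, but the size of the harm is conditional.

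**What to change.** - Analyse baseline, week 12 and week 24 in a linear mixed model by maximum likelihood, with unstructured covariance and group x time x youth. Include every enrolled child in the assigned group, whether or not the programme was completed.
- Make the primary contrast the group difference in change from baseline to week 24. Fix the weighting of the PWS and obese strata in advance (they are allocated 35:10 and 50:20) and report the contrast by stratum as well.
- Reword secondary hypothesis 2 so that it refers to children assigned to the intervention.
- Keep the pre/post completer ANOVA as a sensitivity analysis.
- Confirm that wait-list controls are measured at week 12. The text does not state this separately and the timeline figure is not available here.

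The cost is analysis wording and standard software; no child or visit is added if controls are already measured at week 12. The estimated effect may be smaller than among completers. The model corrects only for drop-out explained by observed data, so loss before week 12 gains nothing from that visit, and loss driven by unobserved outcomes remains a problem. Analysing children as assigned also does not remove bias from allocation by date preference.

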### Curriculum and parental support

The Active Play @ Home curriculum includes age-appropriate goal-oriented physical activities that combine playground and video games with specific exercises that target the following parameters: muscular strength and endurance, aerobic endurance, flexibility, balance, agility, and motor coordination. This curriculum was designed for children ages 8-11 years without disability and children ages 8-15 years with PWS. The curriculum includes playground games and interactive console-based games using the Nintendo Wii™, each of which are to be performed twice weekly. The duration of activity is systematically progressed from 25 to 45 minutes of MVPA over the course of the 24-week intervention. Both the parents and children will be trained to use the curriculum during a hands-on session at baseline. Each family receives the Active Play @ Home manual that contains a daily schedule detailing the activities for each of the four days of the week for the 24 weeks. The manual includes four sections: 1) introduction to the program that includes the philosophy guiding the program, a description of the motor skill and fitness components targeted, and a description of the parent’s role in leading the activities; 2) the daily schedule; 3) detailed descriptions of the playground games; and 4) instructions for playing the interactive console-based games. Each illustrated playground game is accompanied by instructions on how to carry out the activity, as well as instructional cues and modifications to assist the parent in leading the activities for his/her child (See Figure 2). In the interactive console-based games section of the manual we have included instructions on how to set-up the Nintendo Wii™ system and step-by step instructions for playing each of the selected games. Families receive all media equipment necessary as well as a variety of play balls, cones, hoops, foam mats, and boundary markers to be used throughout the intervention.

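### The sample size of 84 rests on a 0.8 SD difference in change, conventionally a large effect, so describing f=.20 as small to moderate misstates what the trial has .95 power to detect

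*Protocol article*

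**What the plan says.** The Data analyses section of the protocol article describes the calculation in a few sentences. The program is named ("A power analysis was performed using G*Power 3.1.9"), the target is set ("to identify the appropriate sample size for a power of .95"), with "an alpha level of .05", and "a correlation between time points was assumed to be .50". The effect, f=.20, is labelled "A small to moderate effect size", and the only reason given is the variability of physical activity expected in children with Prader-Willi Syndrome (PWS). The result is "A sample size of 84 was identified to provide sufficient power to detect an interaction". The paragraph then allows for 30% drop-out and recruits 115.

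It does not say which interaction was meant or which effect-size definition was selected in the program. It does not translate f into a difference in change, in SDs or in units of physical activity. The Study design section gives the allocation: 35 PWS and 50 obese children to intervention (85), and 10 and 20 to wait-list control (30).

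**The concern.** The usual benchmarks for f (.10 small, .25 medium, .40 large) belong to a between-group comparison of means. In a repeated-measures power calculation the f that is entered can sit on a different scale, because the number of measurements and their correlation are applied to it afterwards. The same number then stands for a much larger difference in change than the benchmark suggests.

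This is the only statement of sensitivity for the primary outcome. A reader who takes the label at face value will believe that the trial has .95 power for modest effects. If the label does not match the effect behind 84, that belief is wrong, and a non-significant result could be given more weight against a moderate benefit than the design can bear.

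**Working it through.** **Inputs (Data analyses):** alpha .05, power .95, correlation r = .50, f = .20, pre and post measurements (m = 2), N = 84. **Inputs (Study design):** 85 intervention, 30 control. **Drop-out (Data analyses):** 30%.

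**1. Reproduce 84.** Within-between interaction, k groups, noncentral F with

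λ = f²·N·m/(1−r), df1 = (k−1)(m−1), df2 = (N−k)(m−1).

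With k = 2: λ = .04 × 84 × 2/.5 = 13.44, df = 1 and 82, power = .9518. With N = 83 power is .9496. So 84 is the exact minimum.

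Other settings do not return it:

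| Setting | N for power .95 |
|---|---|
| 2 groups, 2 times, λ = f²Nm/(1−r) | **84** |
| 4 groups, 2 times | 112 |
| 2 groups, 3 times | 66 |
| 4 groups, 3 times | 91 |
| 2 groups, 2 times, correlation already inside f, λ = f²N | 327 |
| same, λ = f²(N−k) | 329 |

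The scale of f can therefore be recovered from the protocol's own figures, although the option chosen is not stated.

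**2. What f=.20 means on that scale.** Let Δ be the difference in mean change between the two groups. In a 2×2 table (group by time) each interaction cell effect is ±Δ/4, so f = Δ/(4·SD) and

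Δ = 4 × .20 × SD = 0.8 SD.

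The SD of change is SD·√(2(1−r)) = SD·√(2 × .5) = SD. At r = .50 the difference is therefore 0.8 on either the outcome scale or the change scale.

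**3. Cross-check.** A two-sample comparison of change, 42 v 42, with d = 0.8 has λ = d²·N/4 = .64 × 84/4 = 13.44 and power .9518, identical to step 1.

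**4. Power of 84 (42 v 42) for smaller differences in change.**

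| Difference in change | Power |
|---|---|
| 0.3 SD | .27 |
| 0.4 SD | .44 |
| 0.5 SD | .62 |
| 0.6 SD | .78 |
| 0.8 SD | .95 |

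The difference detectable at .80 power is about 0.62 SD.

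**5. The planned allocation after drop-out.** 85 × .7 = 59.5 and 30 × .7 = 21.

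- Strata pooled: SE = √(1/59.5 + 1/21) = 0.254 SD.
- PWS and obese strata weighted equally (24.5 v 7 and 35 v 14): SE = ½·√(1/24.5 + 1/7 + 1/35 + 1/14) = 0.266 SD.

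Detectable difference: 0.93 SD (pooled) to 0.97 SD (equal weights) at .95 power, and 0.72 to 0.76 SD at .80 power.

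**The case against.** The strongest reply is that nothing has been miscalculated. The figure 84 follows exactly from the stated inputs, and .20 does lie between the nominal small and medium benchmarks for f. Both points stand. The fault is in the description: the benchmark label does not carry over to the f used here.

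Several stronger readings are tempting, and the document does not support them.

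- *That the value was picked as conservative.* The article says only that it was chosen in view of the variability of physical activity in PWS. It makes no claim of caution, so there is none to rebut.
- *That the trial can find only large effects.* This is fair near .95 power, but not at .80, where the balanced design detects about 0.62 SD.
- *That power for the labelled effect is .44 and that 327 children are needed.* Both figures require reading the label as 0.4 SD with equal arms. The document states neither. The range .27 to .62 is the honest summary.
- *That the program always inflates f² fourfold.* The factor is m/(1−r), which is 4 only because m = 2 and r = .50.
- *That the implied gain is implausible in minutes.* The Curriculum and parental support section says "The duration of activity is systematically progressed from 25 to 45 minutes of MVPA over the course of the 24-week intervention", which invites a comparison with the programme's dose. But no SD is given, and the primary outcome is named only as physical activity. Under an assumed SD of 15 to 25 min/day, 0.8 SD would be 12 to 20 min/day. That is illustration only and carries no weight here.

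It may also be said that the 85:30 split and the drop-out are separate matters from the label. That is right. They enter below only because a corrected sensitivity statement should describe the design as planned.

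**Conclusion.** The point holds as a wrong label on a correct number. Under the calculation that returns 84, f=.20 is a 0.8 SD difference in change between intervention and control, so the stated .95 power does not apply to a small-to-moderate effect. The 0.8 SD is algebra from the protocol's own inputs. It rests only on the inference, from reproducing 84, that the tested effect was the two-group, two-time interaction with the correlation applied outside f.

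The loss of power depends on what the label is taken to mean. For 0.3 to 0.5 SD and equal arms it is .27 to .62, well short of .95 throughout. That a null result would be over-read is a risk, not something the article says.

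**What to change.** In the sample-size paragraph of Data analyses:

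1. Replace the small-to-moderate description by a statement that f=.20, with r=.50 and two time points, corresponds to a 0.8 SD difference in change between groups. Name the interaction tested and the effect-size definition selected in the program.
2. Express that difference in the units of the primary physical activity measure, with the SD used and its source.
3. Add the difference detectable with the planned 85:30 split after 30% drop-out: about 0.93–0.97 SD at .95 power and 0.72–0.76 SD at .80, depending on how the two strata are weighted.

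The cost is a rewording. No participants are added and the analysis does not change. The downside is that the stated sensitivity becomes less favourable.

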## Methods/Design

### Study design

The Active Play @ Home study will evaluate the effectiveness of a 24-week PA intervention on select motor and health–related parameters in children with PWS and children with obesity but without PWS. The study has a quasi-experimental design with semi-random assignment to an intervention group or a wait-listed control group. The intervention group will consist of families with a child with PWS (n=35) and families with a child who is obese (n=50). Ten additional families with a child with PWS will be assigned to a wait-list control group and 20 families with an obese child without PWS will also serve as a wait-list group. Both wait-listed groups will serve as control groups prior to being enrolled in the PA intervention. Groups of two to four families will complete all baseline and follow-up testing on the same day throughout the study. The semi-random assignment consists of a priori established participant cohorts for both intervention and control groups. Upon recruitment, participants will be provided with tentative dates for their visits and their randomization to the cohort (intervention vs. control) will be based on their date preferences. Ethic committee approvals have been obtained from the California State University Fullerton Institutional Review Board and the United States Army Human Research Protection Office. During the first visit, after all study procedures are verbally explained, participants will have time to read the informed assent and consent forms and ask questions regarding the procedures. Afterwards, children participants will sign the informed assent form and their parents or guardians will sign the informed consent form. Figure 1 presents a timeline of the study procedures.

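### The .95 power matches a calculation for two equal groups; with the planned 85:30 split and 30% drop-out it is about .84 to .88

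*Protocol article*

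**What the plan says.** The power paragraph in Data analyses names its software ("A power analysis was performed using G*Power 3.1.9") and its inputs: "for a power of .95, an alpha level of .05 and a correlation between time points was assumed to be .50", and "A small to moderate effect size (*f*=.20) was chosen". Its result is "A sample size of 84 was identified to provide sufficient power to detect an interaction". It then allows for 30% drop-out and sets recruitment at 115. The primary analysis in the same section is a 2 (time) by 2 (group) by 2 (youth) mixed ANOVA using the pre and post measurements.

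Study design fixes the group sizes: "The intervention group will consist of families with a child with PWS (n=35) and families with a child who is obese (n=50"), and "Ten additional families with a child with PWS will be assigned to a wait-list control group and 20 families with an obese child" without PWS. That makes 35 + 50 = 85 intervention and 10 + 20 = 30 control families, 115 in all and about 2.8 to 1. The power paragraph does not mention the unequal split.

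**The concern.** The precision of a comparison between two groups is governed mainly by the smaller one. A power figure computed for equal groups therefore overstates what a 74:26 split of the same total can do. Here the control arm is 30 families before drop-out and about 21 after it, of whom about 7 have a child with PWS.

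What is at stake is how the primary result is read. If the group-by-time interaction is not significant, a reader who takes the .95 at face value will put the chance of having missed an effect of the planned size at 5%. In the design as described it is nearer 12 to 16%.

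**Working it through.** **Inputs.** From Data analyses: alpha .05, target power .95, correlation between time points r = .50, f = .20, N = 84, drop-out 30%, recruitment 115, two time points. From Study design: cells of 35 PWS intervention, 10 PWS control, 50 obese intervention and 20 obese control.

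**Step 1: reproduce the 84.** For a repeated-measures within-between interaction with k equal groups and m time points, λ = f²·N·m/(1 − r), tested on (k − 1)(m − 1) and (N − k)(m − 1) degrees of freedom. With k = 2 and m = 2, λ = .04 × N × 2/.5 = .16N.

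- N = 84: λ = 13.44, F(1, 82), power .952.
- N = 82: λ = 13.12, power .947.

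So 84 is the smallest N that reaches .95. Other set-ups do not give it: four groups at two times need 112, two groups at three times 66, and four groups at three times 91 (92 in equal groups).

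**Step 2: what f = .20 means here.** With equal groups and a difference in change of D (in SDs of change), λ = D²·N/4. Setting this equal to .16N gives D = 0.8. At r = .50 the SD of change is √[2(1 − .5)] = 1 SD of the outcome, so D is also 0.8 SD of the outcome. D = 0.8 is held fixed from here on.

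**Step 3: formulas for the real allocation.**

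- Two-arm contrast: λ = 0.64·n₁n₂/(n₁ + n₂), df = N − 2.
- Equally weighted (Type III) group-by-time term of the 2x2x2 ANOVA: λ = 0.64/V, with V = ¼·Σ(1/n_cell), df = N − 4.

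**Step 4: results.** Drop-out is spread evenly over the cells.

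| Completers | Arms | Two-arm λ | Power | V | Type III λ | Power |
|---|---|---|---|---|---|---|
| 115 (no drop-out) | 85 / 30 | 14.19 | .962 | .0496 | 12.89 | .945 |
| 84 | 62.1 / 21.9 | 10.37 | .889 | .0680 | 9.42 | .858 |
| 80.5 (30% drop-out) | 59.5 / 21 | 9.93 | .876 | .0709 | 9.02 | .843 |

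The last row in full:

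- Two-arm: 59.5 × 21/80.5 = 15.52, and 0.64 × 15.52 = 9.93. In balanced terms this is worth 4 × 15.52 = 62 children.
- Type III: V = ¼(1/24.5 + 1/7 + 1/35 + 1/14) = .0709, and 0.64/.0709 = 9.02. In balanced terms this is worth 4/.0709 = 56 children.
- Type II weighting in the 2x2x2 model lies between the two, at .874.

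**Step 5: separate the two causes.** 115 × 0.70 = 80.5, which is below 84. Recruitment for 30% loss would be 84/0.70 = 120, and 115 tolerates only 1 − 84/115 = 27%. With equal arms, 80.5 completers would still have power .943, so the shortfall alone costs about one point (.952 to .943). The allocation accounts for the rest: .943 to .876 or .843.

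**Step 6: difference detectable at .95.** With 80.5 completers at 85:30, power reaches .95 at D = 0.93 (two-arm) or 0.97 (Type III), against 0.8 in the equal-group calculation.

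**The case against.** Four points deserve weight.

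*The article never says the groups are equal.* True. Equal groups are inferred from the reproduction of 84. The inference is strong, because the other set-ups tried give different numbers, but it should be labelled as such.

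*f could be defined at the actual split.* If f = .20 is taken as an allocation-weighted quantity at 85:30, power with 80.5 completers is about .94 and the allocation costs nothing. That reading requires a larger true difference: D = 0.4/√(.739 × .261) = 0.91 SD instead of 0.8. Conversely, 0.8 SD at this split is an f of about .176. The article gives only f and no raw difference, so holding 0.8 SD fixed is an assumption. It is the sensible one, since the effect of the programme does not depend on how families are divided, but it has to be declared.

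*The loss depends on drop-out and on the term tested.* With no drop-out the two-arm contrast has power .962, above target, and the equally weighted term .945. The .843 rests on Type III weighting, which the article does not specify, and on equal drop-out across cells. This stands, and it is why a range is given. The sentence in the article is about 84 children, however, and at 84 with the planned ratio both versions are below .90.

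*A reader might infer that the trial is underpowered or its primary test unsound.* The documents do not support that. Power is above .80 in every case computed for the planned cells, and unequal allocation as such does not bias the test or change its nominal alpha.

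**Conclusion.** The point holds as a misstatement of the planning figure. The .95 belongs to 84 children in two equal groups. For the design in Study design and the same 0.8 SD difference in change, power is about .86 to .89 with 84 completers, and about .84 to .88 after the plan's own 30% drop-out. The type II error is then 12 to 16% instead of 5%. Allocation causes most of the loss, and the 115-versus-120 shortfall about one percentage point.

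This rests on three assumptions: that the 84 came from the equal-group run, that the effect is held at 0.8 SD of change, and that drop-out is equal across cells. It would be too strong to say that the design cannot have .95 power at all, because the two-arm contrast reaches .962 if nobody drops out. Severity: should-fix.

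**What to change.** Replace the power sentence with one for the real cells, for example:

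> With 85:30 assignment and 30% drop-out (about 80 completers), power to detect a 0.8 SD difference in change (f=.20 under equal groups, r=.50) is about .84 to .88; .95 power is reached for a difference of about 0.93 to 0.97 SD.

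Correct the drop-out arithmetic in the same place: state that 115 allows for about 27% loss to 84, since 30% loss would call for 120.

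The cost is two sentences and a less favourable stated power. No extra participants and no change to the design are needed. Adding the baseline value as a covariate should not be presented as a free way to recover the loss. Cohorts are set by families' date preferences, so the arms may differ at baseline, and a baseline-adjusted analysis and a change analysis can then estimate different things.
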